#### Statistical analyses

Consistent with CONSORT standards [41], the primary analysis will be by intention-to-treat and will be conducted blind to treatment allocation. Baseline data will be secured prior to treatment allocation, and primary analyses will be executed twice: once using observed data, and once using multiple imputation, provided the assumptions for imputation are met [61]. The primary outcome (CBCL Internalising scale) will be analysed first using a 2-sample t-test comparing the intervention and control groups, extended to analysis of covariance (ANCOVA) to control for variation in baseline values. Potentially informative covariates, such as maternal antenatal anxiety, and potential mediators, such as maternal postnatal depression, will also be explored using a general linear model. The impact of the intervention on secondary outcomes, including the Externalising scale of the CBCL, and cognitive and motor development will also be explored using t-tests and ANCOVA. This analytical approach provides a direct and statistically sensitive test of the primary aim. In addition to inferential testing, effect sizes and their associated confidence intervals will be calculated. Finally, univariate logistic regression will be executed to determine any prognostic baseline variables that predict the return or non-return of follow-up data.

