### Randomisation

Women diagnosed with a depressive disorder and meeting all other criteria are offered randomisation after all baseline data are collected. Randomisation is completed by the study co-ordinator in a 1:1 ratio to CBT intervention (n = 115) or to TAU (n = 115), using a pre-generated, variable-length, permuted-blocks allocation schedule, stratified by site, with allocation concealment ensured by central, independent administration consistent with CONSORT standards [41]. The study uses secure randomisation services provided by the NHMRC Clinical Trials Centre. Given the nature of the psychological intervention, study participants cannot be blinded beyond the point of treatment allocation. Outcome assessments are conducted by psychologists who are kept blind to treatment allocation, and the primary analysis will also be conducted blind to treatment allocation. Unblinding is permissible when risk is indicated at follow-up and requires referral to a health professional.

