### Statistical methods

#### Power & Sample size calculations

The study is powered with respect to the primary outcome, the Internalising scale of the CBCL at 24 months. In our pilot data the control group standard deviation (SD) for the Internalising scale was 6.6. For the Internalising scale at 24 months, a between-group (treated vs. non-treated) mean difference of 3.3 points is considered the MCID as it equates to ½ SD difference [58, 59]. With SD = 6.6, the required n to detect a mean difference of 3.3 points in the Internalising scale with 80% power at alpha (two-tailed) = 0.05 is 15.7*(6.6/3.3)*2 = 63 per group. We typically see less than 20% loss to follow-up in our larger perinatal RCTs [48, 60]. For caution, we are allowing for a prudent margin of 25% attrition. This yields n* = 63/(1–0.25)2 = 112 which rounds to 115 per group (n = 230 in total).

A sensitivity analysis in G*Power confirms that with n = 230, both moderate and large effects have high reliability of being detected (power > 90%) and small effects will be reliably detected with power = 70%; even in models including up to six covariates. Thus, the study is sufficiently powered to detect the MCID in the primary child outcome (Internalising scale at 24 months).

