### Trial status and summary

This is an Australian-based randomised trial comparing the emotional and behavioural development of children whose mothers received an 8-week psychological treatment for antenatal depression to children whose mothers received treatment as usual. The protocol has been amended three times as detailed below and the current protocol version is 4 dated 5 August 2021. The trial was registered and approved on the Australian and New Zealand Clinical Trials Registry prospectively in 27 November 2018 and last updated 1 July 2022. Recruitment commenced at site 1 on 29 November 2018, at site 2 on 10 June 2020, at site 3 on 13 September 2021 and at site 4 on 2 November 2022. At the time of manuscript submission, 707 have been referred (self-referred 673, through hospitals 34) to the study, 177 have had a clinical assessment and 102 participants had been randomised to the trial (CBT n = 51; TAU n = 51).

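### Randomisation is stratified by site but the stated primary analysis does not name site; to the extent that site is prognostic, the t-test is mildly conservative

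*Protocol article*

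**What the plan says.** The Randomisation section describes 1:1 allocation "using a pre-generated, variable-length, permuted-blocks allocation schedule, stratified by site". The trial status section gives four opening dates: "Recruitment commenced at site 1 on 29 November 2018, at site 2 on 10 June 2020", then "at site 3 on 13 September 2021 and at site 4 on 2 November 2022".

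Under Statistical analyses, the primary outcome "will be analysed first using a 2-sample t-test comparing the intervention and control groups". This is "extended to analysis of covariance (ANCOVA) to control for variation in baseline values". Beyond that, "Potentially informative covariates, such as maternal antenatal anxiety, and potential mediators, such as maternal postnatal depression, will also be explored" in a general linear model. Secondary outcomes, including the Externalising scale and cognitive and motor development, are also to be analysed by t-test and ANCOVA.

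Site is not named in any of these steps, and nothing in the article says that the analysis will reflect the stratification. The article gives no estimate of how much scores differ between sites.

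**The concern.** Blocking within site forces the arms to be nearly equal in size at every site. Differences between sites then largely cancel out of the treatment comparison, so the true sampling variance of the mean difference excludes most of the between-site variation. A plain two-sample t-test does not know this and leaves that variation in its residual error. If site is prognostic, the t-test reports a standard error larger than the true one.

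At stake is a modest amount of precision in the primary result: a wider interval than the design has earned, a p-value that is slightly too large, and a little lost power. The usual principle is that the primary analysis should carry the factors on which randomisation was stratified, and the stated analysis does not do so.

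**Working it through.** **Inputs from the article (Power & Sample size calculations; Study design).** SD: "the control group standard deviation (SD) for the Internalising scale was 6.6". Target difference 3.3 points (half an SD), two-sided alpha 0.05, power 80%, attrition 25%, 115 randomised per group.

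**The plan's own figure.** 15.7 × (6.6/3.3)² = 15.7 × 4 = 62.8, so 63 per group, as stated. The article then divides by (1 − 0.25)²: 63/0.5625 = 112, rounded up to 115.

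**Number analysed.** 115 × 0.75 = 86.25, so about 86 per group.

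**Assumed input.** R² is the share of outcome variance explained by site. The documents do not give it; 0% to 10% is taken as the range.

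**Formulas** (normal approximation, balance within site kept among those analysed):
- t-test standard error: SE_u = 6.6 × √(2/86) = 1.006.
- True standard error, which the site-adjusted model also reports: SE_a = SE_u × √(1 − R²).
- Overstatement: SE_u/SE_a = 1/√(1 − R²).
- Actual type I error of the t-test: 2 × [1 − Φ(1.96 × SE_u/SE_a)].
- Power without site: Φ((3.3 − 1.96 × SE_u)/SE_a). Power with site: Φ(3.3/SE_a − 1.96).

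| Site R² (assumed) | SE with site | t-test SE too large by | Actual type I error | Power without site | Power with site |
|---|---|---|---|---|---|
| 0% | 1.006 | 0% | 5.0% | 90.6% | 90.6% |
| 2% | 0.996 | 1.0% | 4.8% | 90.9% | 91.2% |
| 5% | 0.981 | 2.6% | 4.4% | 91.2% | 92.0% |
| 10% | 0.955 | 5.4% | 3.9% | 91.8% | 93.3% |

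At R² = 10% the 95% interval half-width falls from 1.96 × 1.006 = 1.97 points to 1.96 × 0.955 = 1.87 points.

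**Check by simulation.** Four sites, permuted blocks of 2, 4 and 6, 230 randomised, 25% missing, 6,000 replicates.
- R² = 10%, even sites: the mean t-test standard error was 1.006 against an empirical SD of the estimate of 0.958. Type I error was 3.9% without site and 4.7% with it; power was 91.6% and 93.3%.
- R² = 10%, one dominant site (200/10/10/10): type I error 3.8% and 4.6%; power 91.0% and 92.7%.
- R² = 5% or less: the simulated type I differences lie within or close to Monte Carlo error, which is √(0.05 × 0.95/6,000) = 0.3 points for each rate.
- R² = 0%: adding site cost almost nothing (even sites: standard error 1.007 against 1.004, power 90.2% against 90.3%).

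**The case against.** **This is analysis-plan detail.** The article is condensed and its SAP is not shown. The ANCOVA covariates are described loosely. In Table 1 the CBCL is collected only at 24 months, so the baseline values cannot be a baseline score of the primary outcome and must be some unlisted set. The power section speaks of models with up to six covariates. A reader might infer that the ANCOVA deliberately excludes site, and the text does not support that: it is silent on site. What stands against the objection is that the article does fix the first test and the order of analyses. The unadjusted t-test is a stated choice, and it does not match the stated design.

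**Site may matter little.** This stands. Of 707 referrals, 673 were self-referred and 34 (4.8%) came through hospitals. The article does not map referral route to randomisation site, and referrals are not randomisations, so what follows is illustrative only. With two strata split 95.2/4.8 and a gap of 0.5 SD between them, R² = 0.952 × 0.048 × 0.5² ≈ 0.011: the standard error is about 0.6% too large and type I error about 4.9%. Reaching R² = 10% would need a gap of about √(0.10/0.0457) ≈ 1.5 SD.

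**Site as a stand-in for pandemic period and delivery mode.** The staggered opening dates might suggest this, but the support is only partial. Telehealth CBT and online questionnaires were trial-wide changes (intervention, outcome measures and CONSERVE-SPIRIT sections), and no site is said to have closed. If site 1 kept recruiting, mode varies within it, and a site term captures mode only in part.

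**The error is on the safe side.** This also stands and limits the weight of the point.

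**Conclusion.** The mismatch is real and minor. Randomisation is stratified by site, and the stated primary analysis does not name it. The consequence is conditional: it exists only to the extent that site predicts the outcome, is nil at R² = 0%, negligible at about 2% or less, and still modest at 10%. A reader might infer that the standard errors are certainly too wide, but the documents give no between-site variance from which to conclude that. Nor do they support any reading that the primary result would be biased, that false positives would be inflated, or that the trial would be underpowered for its target difference. In every scenario examined the t-test is at or slightly below its nominal level, and power at 86 per group stays near or above 90% against a planned 80%.

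The figures assume the pilot SD of 6.6, 25% attrition, four strata, and balance within site largely kept after dropout. The direction of the effect is firm; its size is not known.

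**What to change.** In the Statistical analyses section, add randomisation site as a fixed effect to the ANCOVA of the primary outcome, and name that site-adjusted model as the primary analysis. Do the same in the models for the continuous secondary outcomes. The unadjusted t-test need not be dropped and can stay as a supportive analysis. How to handle a very small site can be left to the SAP.

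The cost is one sentence and at most 3 degrees of freedom for four sites, out of about 170 with 86 analysed per group (2 × 86 − 2). Site should already be held in the randomisation record, so no new data are needed. The change should be made before any outcome data are analysed by arm.

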### Our CBT intervention for antenatal depression and its effect on child development

Our antenatal CBT treatment for depression, Beating the Blues Before Birth, has been trialled and validated for its effect on child development in a pilot study [22]. In a feasibility study, the treatment has proved to be highly effective at reducing both depression and associated anxiety in a population of pregnant women diagnosed with depression (80% with major depressive disorder) [22]. The pilot RCT that followed is to our knowledge one of only a very few published trials reporting the impact of antenatal depression treatment on child behavioural outcomes [22]. In this pilot RCT (n = 54), substantial reductions were achieved in maternal depression and anxiety in the intervention group compared to TAU. Depression gains were maintained at 9 months postpartum (Cohen’s d = 0.67, p = .05). The intervention group showed excellent treatment adherence. Of a possible eight sessions, women in the intervention attended an average of 6.30 (SD 2.91); 78% attended six or more sessions, and 63% completed all eight sessions. At 9 months, the largest effects [29] on child outcomes were seen on the Infant Behaviour Questionnaire-Revised (IBQ-R: [30]) including subscales measuring negative affectivity (d = 0.84, p = .03) and stress reactivity (d = 1.08, p = .007). Stress reactivity in infants is a specific area that is impacted negatively by maternal mental health difficulties in pregnancy [31]. Several subscales of the Ages & Stages Questionnaire-3 and Ages & Stages Questionnaire Socio-Emotional (ASQ-3 and ASQ-SE: [32], [33]) also showed large effects favouring the intervention group children at 9 months including self-regulation (d = 0.83, p = .03) and communication (d = 0.81, p = .04). Our follow-up study in this cohort demonstrated differences in child behaviour at 24 months [23]. On the CBCL [34], medium-to-large effect sizes [29] were seen in behaviours comprising the Internalising scale, especially ‘withdrawal’ and ‘anxious/depressed’ behaviours (d = 0.57 and 0.59 respectively) and in emotional self-regulation (d = 0.42). Intervention group children also trended towards lower scores (d = 0.5) on the DSM-oriented Anxiety Problems scale (which maps CBCL items to DSM anxiety diagnoses). Furthermore, five out of seven syndrome subscales showed a trend in favour of the intervention group. Motor and cognitive development (assessed with the Bayley Scales: [35]) showed small-to-medium sized effects in the same direction (d = 0.52 and d = 0.26 respectively). While highly encouraging, our pilot work was based on a relatively small sample and the current protocol describes a fully-powered study capable of reliable statistical detection of a MCID in early child behavioural problems. To our knowledge this is the first adequately-powered study with medium-term follow-up to determine whether effectively treating maternal depression exclusively in pregnancy has a beneficial effect on child outcomes.

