##### Criteria for discontinuing the intervention

Given this is an antenatal intervention it is discontinued when participants give birth prior to the completion of the 8 sessions, in which case a final single postnatal session is delivered prior to the 3-month post-birth time point.

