## Discussion

Maternal depression in pregnancy is highly prevalent and can have negative consequences on child emotional and behavioural development. Therefore, effectively treating depression in pregnant women can potentially prevent adverse emotional and behavioural development outcomes in their children. Our previous studies have demonstrated the effectiveness of our CBT intervention at reducing maternal depressive and anxiety symptoms during pregnancy [22] and showed promising results with respect to amelioration of child outcomes in our previous pilot study [22] and follow-up study [23]. The current RCT is adequately powered to detect the MCID in child internalising behaviour at 24 months following CBT intervention in pregnancy. CBCL internalising scores in early childhood are known to correlate with later mental health disorders [36, 37].

Susceptibility to emotional and behavioural problems in children of antenatally depressed mothers is thought to be exerted by antenatal and postnatal mechanisms as postulated by the model of Goodman and Gotlib [62]. The antenatal mechanism thought to mediate this susceptibility is dysfunctional neuroregulation due to fetal programming. This is supported by substantial evidence demonstrating the contribution of antenatal depression-induced alterations in the in-utero environment in predisposing the child to risk of psychopathology e.g., through changes in the hypothalamic–pituitary–adrenal axis function [17, 18] and other biological systems. Another biological mechanism underpinning this susceptibility suggested in the model is genetic predisposition. However, whilst the offspring’s DNA sequence is permanent, neuroregulation is shaped by the in-utero environment and could therefore conceivably be altered by antenatal psychological interventions (for instance if the intervention had a downstream effect on biological systems involved in programming e.g., cortisol levels [63]).

If our hypothesis that treating maternal depression in pregnancy can prevent adverse child outcomes is confirmed, this will contribute to our understanding of the impact of the in-utero environment on child outcomes and will have significant repercussions for standard antenatal care. In addition, this will better inform the delivery of maternal and infant health services and research into the prevention of the intergenerational transmission of mental health disorders.

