Potential limitations: Given this is an RCT it is not possible to control for possible confounding influences that happen after randomisation, including postnatal influences such as maternal depression severity.

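### Postnatal depression is a potential mediator, not a confounder; a linear model adjusted for it gives a direct effect only under strong assumptions, and the total effect does not isolate the in-utero route

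*Protocol article*

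**What the plan says.** - **Protocol article, Statistical analyses.** The primary outcome is analysed by intention to treat, with a two-sample t-test and then ANCOVA on baseline values. The section then adds that "potential mediators, such as maternal postnatal depression, will also be explored using a general linear model". Maternal antenatal anxiety is named in the same sentence as an example of an informative covariate.
- **Discussion, potential limitations.** Because the trial is randomised, "it is not possible to control for possible confounding influences that happen after randomisation, including postnatal influences such as maternal depression severity".
- **Discussion, main text.** If the hypothesis is confirmed, "this will contribute to our understanding of the impact of the in-utero environment on child outcomes". The same part of the Discussion names both antenatal and postnatal mechanisms for the child's risk. The Background draws a similar inference about fetal programming, worded more cautiously as consistency.
- **Background, section on the CBT intervention.** The study is to show whether "effectively treating maternal depression exclusively in pregnancy has a beneficial effect on child outcomes". The same section reports that pilot depression gains persisted at 9 months postpartum (d = 0.67, p = .05; pilot n = 54).
- **Criteria for discontinuing the intervention.** For women who give birth before finishing the eight sessions, "a final single postnatal session is delivered prior to the 3-month post-birth time point".

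**The concern.** One post-randomisation variable has two incompatible roles: a mediator to be modelled, and a confounder that cannot be controlled. A confounder of a randomised comparison would have to influence allocation, and maternal mood after birth cannot do that. On the pilot's evidence it is a consequence of treatment and so may lie on the path to the child's score.

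The role decides what the general linear model can deliver. Randomisation protects the treatment-to-mediator and treatment-to-outcome relations, but not the mediator-to-outcome relation. Common causes of maternal mood and the CBCL score therefore enter once postnatal depression is in the model. A shared informant is one plausible source: the BDI-II is the mother's own report, the CBCL is completed by a parent or other caregiver, and Table 1 schedules both at 24 months.

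At stake is the mechanistic conclusion. The trial may find a real benefit to children that arises partly or wholly because mothers stay less depressed after birth. Neither the total effect nor a simply adjusted coefficient shows how much arose in utero.

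**Working it through.** **1. The plan's own figure.** Inputs from Power & Sample size calculations: "In our pilot data the control group standard deviation (SD) for the Internalising scale was 6.6"; a "mean difference of 3.3 points is considered the MCID"; "80% power at alpha (two-tailed) = 0.05". Then 15.7 × (6.6/3.3)² = 62.8, so 63 per group; 63/(1 − 0.25)² = 112, rounded up to 115. The stated figures reproduce. They rest on a comparison without postnatal depression, so nothing below changes them.

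**2. The linear mediation identity.** Let a be the effect of treatment on postnatal depression, b the causal slope of the child score on it, δ the extra slope from unmeasured common causes, and ρ the mediator's reliability, all in SD units. Multiply by 6.6 for CBCL points.

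- Total effect = direct + a·b
- Coefficient adjusted for the mediator = direct − a·δ (mediator measured without error)
- With reliability ρ and δ = 0, the adjusted coefficient = direct + a·b·(1 − ρ)

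The pilot gives a = −0.67. The documents give no b, δ or ρ, so these are assumed over ranges.

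**3. Can the postnatal route alone produce a total effect?** Set the direct effect to zero:

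| b (assumed) | a·b × 6.6, points | Share of 3.3 |
|---|---|---|
| 0.1 | −0.44 | 13% |
| 0.3 | −1.33 | 40% |
| 0.5 | −2.21 | 67% |

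The full 3.3 points would need b = 0.50/0.67 = 0.75. The postnatal route can thus supply part of an observed effect with nothing happening in utero.

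**4. Is the adjusted coefficient the direct effect?**

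- With δ = 0 and no mediator error, yes.
- With δ = 0.05 to 0.3, it shifts by 0.67 × 0.05 × 6.6 = +0.22 to 0.67 × 0.3 × 6.6 = +1.33 points, which understates a beneficial direct effect.
- With δ = 0, b = 0.2 to 0.4 and ρ = 0.9 to 0.7, it retains −0.67 × 0.2 × 0.1 × 6.6 = −0.09 to −0.67 × 0.4 × 0.3 × 6.6 = −0.53 points of the postnatal path, which overstates it.

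**5. Simulation check** (1,000,000 records, a = −0.67, b = 0.3). The common cause loads 0.45 on both mediator and outcome, so δ = 0.45² ≈ 0.20.

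| True direct | Common cause | ρ | Total | Adjusted |
|---|---|---|---|---|
| −1.98 | none | 1 | −3.31 | −1.98 |
| −1.98 | present | 1 | −3.31 | −1.08 |
| 0 | none | 1 | −1.34 | −0.01 |
| 0 | present | 1 | −1.33 | +0.90 |
| 0 | none | 0.8 | −1.31 | −0.25 |

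The simulation agrees with the identity: no bias when the assumptions hold, and bias in either direction when they fail.

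**The case against.** The plan has a fair defence. The analysis section uses the right word, mediator, and says only that such variables will be explored. A general linear model is an ordinary framework for regression-based mediation, and a condensed article may leave the instrument, visit and confounder set to the analysis plan. The limitations sentence may mean only that the design cannot govern what happens after birth, and as a stated limitation it partly concedes the point. The single postnatal session is an exception for women who deliver early.

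Much of this stands. The missing mediation detail is not held against the article, and the session is a minor wording matter. What does not stand is calling a treatment-affected variable a confounder of the randomised comparison.

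Three stronger readings are tempting but unsupported:

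- **That the adjusted estimate is biased outright.** Bias depends on confounding, interaction or mediator error, and is zero without them.
- **That the fall from the total to the adjusted coefficient measures bias or costs the trial power.** With a total effect of 0.50 SD, a mediator difference of 0.67 SD and an assumed slope of 0.4, the coefficient becomes 0.50 − 0.67 × 0.4 = 0.23 SD. If that slope is causal, 0.23 SD is the true direct effect: this is assumed mediation, not bias. The primary comparison never uses this coefficient.
- **That the authors will present the adjusted estimate as the fetal programming effect.** The Background does reason this way about cohort studies, taking associations that survive adjustment for postnatal depression as pointing to an in-utero origin. For this trial, however, both the Background and the Discussion tie the in-utero reading to the treatment hypothesis being supported, which is the total effect.

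**Conclusion.** The concern holds in a limited form. The limitations sentence is wrong as written, and the two sections must agree that postnatal depression is a potential mediator. A coefficient adjusted for it answers a different question from the randomised comparison, and answers it without bias only under assumptions that randomisation does not secure. The total effect combines antenatal and postnatal routes, so the Discussion's in-utero sentence claims more than the design can separate.

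The illustrated size is a shift of +0.22 to +1.33 points from confounding, or −0.09 to −0.53 points from mediator error, against a target difference of 3.3. A postnatal route alone would yield −0.44 to −2.21 points. These figures rest on a linear model, on assumed b, δ and ρ, and on d = 0.67 from a pilot of 54 women. They show what is possible and do not predict what the trial will find. The primary analysis, its alpha, the sample size and the power stand as planned.

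**What to change.** 1. Keep post-randomisation variables out of every model reported as the treatment effect.
2. For mediators, replace the general linear model with a mediation analysis labelled exploratory. Use a mediator measured before the outcome (the 3-month BDI-II or the blinded 3-month SCID). Adjust for baseline BDI-II, baseline BAI, depression history and site, and allow for a treatment-by-mediator interaction. State the assumptions and add a sensitivity analysis for unmeasured mediator-outcome confounding.
3. In the limitations paragraph, describe postnatal depression as a potential mediator.
4. In the Discussion, state that the randomised comparison estimates the combined effect by antenatal and postnatal routes.
5. Reconcile the description of treatment as confined to pregnancy with the postnatal session.

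The cost is some wording and one exploratory analysis on data already scheduled. The downside is a weaker mechanistic claim. A 3-month measure also captures only part of postnatal depression, so even a sound direct-effect estimate would not by itself be an in-utero effect.
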